#### Data collection and management

Instruments and questionnaires for data collection are listed in Table 1. Data will be entered into REDCap and, to promote excellent data quality, double data entry by two independent data entry clerks will be performed.

### Planned refinement of the PINGS program

We will refine the PINGS content, delivery format and feedback mechanisms for initial and sustained use, based on subjects’ adherence data, responses to adherence feedback, providers’ responses and other variables that might influence optimal use of the PINGS study [59, 60]. We propose that, over time, positive feedback (including immediate BP feedback, medication adherence feedback, motivational/reinforcement messages) will create sustained behavior change. Although insufficiently powered for formal mediation analyses, we will explore relationships via structural equation modeling using self-determination theory constructs of subjects’ competence (Competence Scale scores) and autonomous regulation (Autonomous Self-Regulation Scale scores) with changes in primary clinical outcomes (changes in BP control, BP and medication adherence), which will help guide further PINGS’ refinement. Providers’ and patients’ attitudes and treatment satisfaction play important roles in the degree to which an intervention is adopted [61–63]. This information will guide how PINGS is presented to the Ghanaian health care community assuming that the feasibility trial and future efficacy/effectiveness RCTs are successful.

### Statistical analyses

#### Feasibility outcomes

We will use 95 % confidence intervals (CIs) for proportions to estimate dichotomous outcomes (e.g., proportion agreeing to participate); adherence to protocol (e.g., use of a medication pill tray, use of a smartphone to send BP measurements, opening of SMS/voice mail messages, and so forth). Frequency distributions will be developed describing reasons for provider and patient protocol nonadherence, dropout and problems encountered such as technology glitches, medication side effects, and so forth. For continuous measures (e.g., patient satisfaction scores), frequency distributions and median and mean responses (with 95 % CIs) will be used. Chi-square tests (categorical measures) and pooled *t* tests (or Wilcoxon rank sum tests) for continuous measures will compare intervention group and SC groups.

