**Methods:**

This two-arm cluster randomized controlled feasibility pilot trial will involve 60 recent-stroke survivors. Using a computer-generated sequence, patients will be randomly allocated into four clusters of 15 patients each per physician: two clusters in the intervention arm and two in the control arm. Patients in the intervention arm will receive a simple pillbox, a Blue-toothed UA-767Plus BT BP device and smartphone for monitoring and reporting BP measurements and medication intake under nurse guidance for 3 months. Tailored motivational text messages will be delivered based upon levels of adherence to the medication intake. Both groups will be followed up for 6 months to compare BP control at months 3, 6 and 9 as primary outcome measure. Physicians assessing BP control will be blinded to arms into which patients are allocated. Secondary outcome measures will include medication adherence scores and Competence and Autonomous Self-regulation Scale scores. A qualitative study is planned after follow-up to explore the lived experiences of participants in the intervention arm.

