## Methods

### Trial design

This is a two-arm cluster randomized controlled trial involving 60 stroke survivors with the physician as unit of randomization and patients as unit of analysis. Each of the four physicians will be recruited and randomly assigned to the intervention or control group by the statistician (who is not involved in provider or patient recruitment nor data collection) using a computer-generated random sequence. Four groups/clusters of 15 eligible patients will be assigned to either control or intervention arms by the study coordinator after having met study criteria for enrollment (Fig. 1). A cluster randomized trial has been chosen to avoid potential treatment contamination in which physicians might unintentionally provide patients with different degrees of attention or blending of treatment protocols. The checklist for the study protocol is provided as Additional file 1.

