### Follow-up phase

Subjects in both arms of the study will be followed up for 6 months after the initial 3-month trial. During the follow-up period, subjects will attend clinics monthly where their physicians will assess them clinically. At months 3, 6 and 9 post enrollment patients and providers will undergo assessments on methodological parameters and consumer responses, clinic BP measurements, medication adherence, health literacy on stroke and HTN as well as self-determination theory constructs such as Autonomous Self-regulation and Competence Scales. Physicians in both groups will also undergo assessment on adherence to BP management protocols (Fig. 1 and Table 1).

**Table 1 Tab1:** Study outcome measures

Outcomes	Psychometrics (internal consistency [α], test-retest reliability [r]) NOTE A^a^	Time points
Primary outcomes		
Feasibility: methodological parameters and consumer responses	Recruitment and retention rates; Self-report: Patient/Provider Satisfaction Scale (.82–.96, test-retest (1 week) .98) [74, 75], fidelity checklists: patient level (e.g., connection; BP uploads via phone; opening of messages/educational information and provider level (e.g., delivery of provider summaries; phone alerts)	Baseline, 3, 6, 9 months
Clinic: BP	Clinic-based BP	
Feedback and refinement	Focus groups	Providers and IG: 9 months
Secondary outcomes		
Medication adherence Physician adherence	Medication Possession Ratio (MPR); Morisky Medication Adherence Scale (α = .76–.83, r = .64) [76, 77], provider guideline adherence: timely med changes (date of script changes following BP feedback (bi-monthly PINGS reports/clinic BPs)	Baseline, 3, 6, 9 months
Self-determination theory constructs	Autonomous Self-Regulation (α = .81–.84, r = .38) [78], Competence Scale (α = .88–.95, r = .32–.46) [51, 52, 78].	
Potential moderators/mediators		
Demographics	Age, education level, income	Baseline
HTN/stroke knowledge, health literacy, anthropometrics	Self-report: HTN/stroke knowledge (.70) [54, 55], health literacy (r = .74, .82) [78–80], Height/ weight/girth	Baseline, 3, 6, 9 months
Medication adherence factors	Side effects, adverse events	As reported, and 3, 6, 9 months

^a^Basic psychometric property analyses (e.g., internal consistency, test-retest reliability) will be conducted during first 3 months on scales, which have not been used with Ghanaian stroke patients

*BP* blood pressure, *HTN* hypertension, *IG* Intervention Group

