#### Proposed sample size

For this feasibility cluster RCT we will recruit 15 patients per cluster (i.e., physician), 30 patients per group (intervention versus control group) (total *n* = 60). We agree with Kraemer et al. [57] that pilot feasibility studies are deficient in estimating effect size with sufficient accuracy for future study design. To this end we will evaluate the availability of subjects, assess proportions approached/consented, and examine the feasibility of PINGS by evaluating adherence and retention rates. Thus, sample size justification focuses on the precision of estimates rather than the power of statistical tests. We will recruit 30 subjects (15 per physician = cluster) per treatment group based on number of degrees of freedom within each cluster, as suggested by Mead, to obtain reasonable precision for variance estimates [58].

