#### Primary outcome measures

For these measures, generalized linear mixed models (GLMM) will be used to compare the two groups with group as primary independent variable and percent success reaching BP control (or resting BP changes individually) as the primary dependent variable (Table 2) [64]. GLMM allow for missing data, measurement at different times and take into account the effect of clustering, i.e., correlation of repeated measurements within patients clustered within MD (Medical Doctor) provider. Group and time (baseline, 3, 6 and 9 months) will be fixed effects; demographics and secondary outcome measures (e.g., medication adherence via the MPR) will be adjustment covariates. We will assess changes over time via a time-by-intervention interaction term in multivariable models. We will estimate differences (for means or proportions) in ancillary moderator and mediator measures between the two groups via 95 % CIs as appropriate (e.g., self-efficacy, autonomous regulation, and so forth.). We will estimate differences (via 95 % CI) in proportions and average slopes between intervention versus control groups and evaluate linearity of trajectories as input for future RCT analysis strategy. We will estimate percent success reaching BP control for each subject over the trial (baseline, 3, 6 and 9 months), and the within-subject longitudinal trajectories (e.g., slopes), and then summarize as mean longitudinal trajectory within each treatment group (e.g., mean slopes with 95 % CI). Intracluster correlation coefficient (ICC) and variance estimates will be obtained of efficacy outcomes and covariance structure of the longitudinal scores for determination of sample size (and hence adequate power) for a future RCT. Multiple imputation methods will be used for missing end-of-study outcomes. Dropout rate, both selective and differential, is an important issue. If more than 10 % of data are missing, we will add an intermediate evaluation point in a future RCT to provide more data for use in endpoint imputation.

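### Feasibility outcomes are compared between arms with patient-level tests that ignore the four randomised physicians, so for any positive intracluster correlation the p-values are too small

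*Protocol article*

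**What the plan says.** All references are to the protocol article.

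- **Design.** Trial design describes a cluster trial "with the physician as unit of randomization and patients as unit of analysis". The abstract gives "two clusters in the intervention arm and two in the control arm", and Proposed sample size gives "15 patients per cluster (i.e., physician), 30 patients per group (intervention versus control group".
- **Basis of the sample size.** Proposed sample size states that "sample size justification focuses on the precision of estimates rather than the power of statistical tests".
- **Feasibility analysis.** Statistical analyses, Feasibility outcomes, plans 95% confidence intervals and then names the between-arm tests: "Chi-square tests (categorical measures) and pooled" t tests, "or Wilcoxon rank sum tests) for continuous measures will compare intervention group and SC groups". No physician term or cluster adjustment is mentioned.
- **Other outcomes.** The next two statistical sections use generalized linear mixed models. For blood pressure these are said to allow for patients clustered within physician. For secondary outcomes the physician is a random effect.
- **Status.** Table 1 puts "Feasibility: methodological parameters and consumer responses" under primary outcomes. The Outcome measures section instead gives feasibility its own heading, apart from the primary outcome measures.

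**The concern.** When physicians are randomised, the difference between arms carries the variation between physicians as well as that between patients. Chi-square, pooled t and rank sum tests use only the patient-level variation. (Pooled here refers to one variance shared by the two arms and does nothing about clusters.) If satisfaction or retention differs between physicians for reasons unrelated to PINGS, part of that difference falls between the arms by chance, and the tests will too often call it an effect of the intervention.

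The protocol recognises the issue for its other outcomes, so the feasibility section is out of line with the rest of the plan. What is at stake is the reading of a pilot that is meant to inform a larger trial: a satisfaction or retention difference could look established when four physicians cannot establish it.

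**Working it through.** **Inputs from the protocol.** 4 physicians, 2 per arm, m = 15 patients per physician. The stated sample size reproduces: 4 × 15 = 60 in total and 2 × 15 = 30 per arm. There is no power calculation to reproduce.

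**Assumptions.** A two-sided 5% level, and ICC values of 0.01 to 0.10, because the protocol gives neither for these outcomes.

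**Formulas.**
- Design effect: DE = 1 + (m − 1) × ICC = 1 + 14 × ICC.
- Effective patients per arm: 30 / DE.
- True size of a nominal 5% test: 2 × (1 − Φ(1.96 / √DE)).

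Example at ICC 0.05: DE = 1 + 14 × 0.05 = 1.70; √1.70 = 1.30; 1.96 / 1.30 ≈ 1.50; size = 13.3%. Effective sample: 30 / 1.70 = 17.6 per arm, about 35 of the 60.

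The formula was checked by simulating null trials with two clusters of 15 per arm: 40,000 per ICC for the t and chi-square tests, 4,000 for Wilcoxon.

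| ICC (assumed) | DE | Effective n per arm | Size, formula | Size, pooled t (simulated) | Size, Wilcoxon (simulated) |
|---|---|---|---|---|---|
| 0 | 1.00 | 30.0 | 5.0% | 4.9% | 4.7% |
| 0.01 | 1.14 | 26.3 | 6.6% | 6.7% | 6.3% |
| 0.02 | 1.28 | 23.4 | 8.3% | 8.2% | 7.7% |
| 0.05 | 1.70 | 17.6 | 13.3% | 13.6% | 12.0% |
| 0.10 | 2.40 | 12.5 | 20.6% | 21.4% | 20.0% |

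**Chi-square.** The result depends on the scale on which the ICC is defined. With beta-binomial data at an 80% rate, where the ICC is on the scale of the outcome itself, the size is 8.3%, 13.6% and 21.4% at ICC 0.02, 0.05 and 0.10. With the ICC on an underlying normal scale and a 50% rate, it is 7.4%, 10.5% and 15.8%. The direction is the same and the second set is milder.

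**Valid comparator.** In the same simulations, a t test on the four physician means (2 df) had a size of 4.8% to 5.1% at every ICC.

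**Price of validity.** The 95% half-width for a difference in means, in SD units:
- ignoring clusters: 2.00 × √(2/30) = 0.52;
- with clusters: 4.30 × √(2/30 × DE) = 1.19, 1.45 and 1.72 at ICC 0.01, 0.05 and 0.10.

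Most of the widening comes from having 2 df instead of 58: at ICC 0 the 2-df half-width is already 1.11.

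**The case against.** **Small ICC.** All 60 patients attend one neurology clinic, so a shared clinic cannot separate the physicians. Much of PINGS is delivered by app, text message and nurse. Allocation and concealment also describes randomising subjects in blocks of four, which would remove systematic case-mix differences between physicians. This stands as a limit on size: near ICC 0 the tests are close to nominal. It does not make them valid. That section conflicts with Trial design and the two must be reconciled, but under either text patients are nested in four physicians, two per arm, and anything a physician does after allocation is shared by that physician's patients.

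**Scope.** The only continuous measure named as an example in the feasibility analysis is patient satisfaction. Dropout is mentioned there only through frequency distributions of its reasons. Pill-tray use and blood pressure uploads belong to the intervention arm and have no control counterpart. This stands, and is why the point is confined to measures that exist in both arms.

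**Consequence.** The sample size rests on precision, and no progression rule uses these p-values. Primary status comes from Table 1 alone, while the abstract names blood pressure control as the primary outcome. This tempers the importance. It also means that the tests serve no stated purpose.

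**Detail left to the analysis plan.** This is a fair answer for the confidence intervals, since no formula is given. It is no answer for the tests, which are named.

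**Two stronger readings are tempting but not supported.**
- A reader might infer that the slope intervals under Primary outcome measures, where the plan will "summarize as mean longitudinal trajectory within each treatment group", share the fault. That text follows directly on a mixed model said to handle clustering and gives no interval formula, so a fault is not shown.
- A reader might infer that provider satisfaction will be tested with two physicians against two. The sentence naming the tests does not say so; that requires combining it with the separate list of feasibility outcomes.

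**Conclusion.** The concern holds for the named between-arm tests on post-allocation feasibility outcomes: clearly for patient satisfaction, and for retention or protocol adherence where both arms have data and are tested. These tests do not fit a design with two physicians per arm, and they depart from the protocol's own treatment of its other outcomes. The excess false-positive rate depends on an ICC that the protocol does not give. For the pooled t test it runs from slight (6.7% at 0.01) to about fourfold (21% at 0.10). The direction is certain for any positive ICC. The conclusion does not depend on feasibility being a primary outcome, and it does not extend to the blood pressure or secondary analyses.

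**What to change.** In Statistical analyses, Feasibility outcomes:

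1. Delete the chi-square, pooled t and Wilcoxon comparisons for outcomes measured after allocation. Report these outcomes descriptively by physician and by arm.
2. If a between-arm contrast is wanted, base it on the four physician means (difference of arm means, t on 2 df), or use the physician random-effect model already planned for secondary outcomes with a small-sample correction to the degrees of freedom.
3. State that any 95% interval for a post-allocation outcome allows for clustering. The 2 df belong to the between-arm contrast; an interval for one arm built from its own two physician means has only 1 df.
4. Keep ordinary binomial intervals for approach and consent rates, which precede allocation.

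The cost is a change of wording, little programming, and much wider intervals for any formal contrast. At ICC 0.05 the half-width for a difference in means goes from 0.52 to 1.45 SD. That is what two physicians per arm can support, and it is a reason to prefer the descriptive report.

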#### Primary outcome measures

For these measures, generalized linear mixed models (GLMM) will be used to compare the two groups with group as primary independent variable and percent success reaching BP control (or resting BP changes individually) as the primary dependent variable (Table 2) [64]. GLMM allow for missing data, measurement at different times and take into account the effect of clustering, i.e., correlation of repeated measurements within patients clustered within MD (Medical Doctor) provider. Group and time (baseline, 3, 6 and 9 months) will be fixed effects; demographics and secondary outcome measures (e.g., medication adherence via the MPR) will be adjustment covariates. We will assess changes over time via a time-by-intervention interaction term in multivariable models. We will estimate differences (for means or proportions) in ancillary moderator and mediator measures between the two groups via 95 % CIs as appropriate (e.g., self-efficacy, autonomous regulation, and so forth.). We will estimate differences (via 95 % CI) in proportions and average slopes between intervention versus control groups and evaluate linearity of trajectories as input for future RCT analysis strategy. We will estimate percent success reaching BP control for each subject over the trial (baseline, 3, 6 and 9 months), and the within-subject longitudinal trajectories (e.g., slopes), and then summarize as mean longitudinal trajectory within each treatment group (e.g., mean slopes with 95 % CI). Intracluster correlation coefficient (ICC) and variance estimates will be obtained of efficacy outcomes and covariance structure of the longitudinal scores for determination of sample size (and hence adequate power) for a future RCT. Multiple imputation methods will be used for missing end-of-study outcomes. Dropout rate, both selective and differential, is an important issue. If more than 10 % of data are missing, we will add an intermediate evaluation point in a future RCT to provide more data for use in endpoint imputation.

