## Abstract

**Background:**

Hypertension is the premier modifiable risk factor for recurrent stroke. In sub-Saharan Africa (SSA) where the stroke burden is escalating, little is known about the role of behavioral interventions in enhancing blood pressure (BP) control after stroke.

Our objective is to test whether an m-Health technology-enabled, nurse-led, multilevel integrated approach is effective in improving BP control among Ghanaian stroke patients within 1 month of symptom onset compared with standard of care.

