#### Secondary outcome measures

These are categorical (percent of patients and providers who were adherent) and continuous (e.g., MPR, MMAS score; Competence and Autonomous Self-regulation Scale scores). GLMM will compare the two groups with treatment group as primary independent variable, and outcome measures individually as the dependent variables [64]. Group and time (baseline, 3-, 6- and 9-month visit) will be included as fixed and physician as random effects; health literacy, demographics (age, gender, and so forth) and HTN/stroke knowledge will be adjustment variables. Ninety-five percent CIs will be reported.

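### With two physicians per arm, the feasibility tests ignore physician, and the pilot ICC is too imprecise to size the next trial

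*Protocol article*

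**What the plan says.** Under Trial design, "Each of the four physicians will be recruited and randomly assigned to the intervention or control group by the statistician". The Abstract confirms "two clusters in the intervention arm and two in the control arm", and Proposed sample size gives 15 patients per physician, 30 per arm and 60 in all.

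Four statements bear on clustering:

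- **Statistical analyses, Feasibility outcomes.** Chi-square tests are named for categorical measures. For continuous ones the plan is pooled t or "Wilcoxon rank sum tests) for continuous measures will compare intervention group and SC groups". No physician term is mentioned. Table 1 places feasibility under primary outcomes.
- **Statistical analyses, Primary outcome measures.** The model is described so: "GLMM allow for missing data, measurement at different times and take into account the effect of clustering", with repeated measurements nested in patient and patient nested in physician. The section adds: "Intracluster correlation coefficient (ICC) and variance estimates will be obtained of efficacy outcomes", for use in determining the sample size of a future trial.
- **Proposed sample size.** The number per physician is justified by degrees of freedom within each cluster, "to obtain reasonable precision for variance estimates".
- **Statistical analyses, Secondary outcome measures.** Group and time "will be included as fixed and physician as random effects".

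The Abstract states the aim as a test: "Our objective is to test whether an m-Health technology-enabled, nurse-led, multilevel integrated approach is effective in improving BP control".

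**The concern.** Arm does not vary within a physician, so a difference between arms is also a difference between two pairs of physicians. Only 2 degrees of freedom, one per arm, show how far physicians differ by chance. If patients are instead allocated to clusters as Allocation and concealment describes, physicians are still nested in arm and the limit is the same.

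Two consequences matter. A feasibility comparison that treats the 60 patients as independent can report a chance difference between physicians, for example in satisfaction or retention, as an effect of the intervention. And an ICC from four physicians, used as a planning value, could mis-size the definitive trial badly in either direction. Proposed sample size concedes that pilots estimate effect size poorly, but the protocol makes no such concession for the ICC.

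**Working it through.** **Inputs.** From the protocol: 4 physicians, 2 per arm, m = 15 patients each. Check: 4 × 15 = 60 in total and 2 × 15 = 30 per arm, as stated. The protocol gives no ICC, so 0.01 to 0.10 is assumed. Between-physician df within arm: 2 × (2 − 1) = 2. Within-physician df: 4 × (15 − 1) = 56, or 14 per physician.

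**1. Tests that ignore physician.** The design effect is DE = 1 + (m − 1) × ICC. A test that assumes independence understates the variance of the arm difference by this factor, so its error is roughly 2 × [1 − Φ(1.96/√DE)]. The simulations cover one time point with no true arm effect; the binary outcome has a proportion of 0.5.

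| ICC | DE | Formula | Simulated pooled t | Simulated chi-square | t on physician means, 2 df |
|---|---|---|---|---|---|
| 0.01 | 1.14 | 6.6% | 6.6% | 6.8% | 5% |
| 0.02 | 1.28 | 8.3% | 8.4% | 8.7% | 5% |
| 0.05 | 1.70 | 13.3% | about 13% | 14.0% | 5% |
| 0.10 | 2.40 | 20.6% | about 21% | 21.9% | 5% |

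Valid limits are wide. For a mean difference in SD units, the half-width is about t × √(2 × DE/30). Ignoring physician: 2.00 × √(2/30) = 0.52. With 2 df (t = 4.30): 1.19 at ICC 0.01, 1.45 at 0.05 and 1.72 at 0.10. For a difference in proportions near 0.5, ±25 percentage points becomes about ±59 at ICC 0.01 and ±72 at ICC 0.05.

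**2. Precision of the ICC.** Let F be the between-physician (within arm) mean square over the within-physician mean square. An observed ICC of r corresponds to F = 1 + 15r/(1 − r). The exact limits divide F by the F(2, 56) quantiles 3.943 and 0.0253, then convert back by (F − 1)/(F + 14).

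For r = 0.05: F = 1.789. Lower limit: 1.789/3.943 = 0.454, giving −0.04, that is, zero. Upper limit: 1.789/0.0253 = 70.6, giving 69.6/84.6 = 0.82.

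| Observed ICC | 95% interval (lower limit cut at 0) | Design effect at m = 15 |
|---|---|---|
| 0.01 | 0 to 0.75 | 1 to 11.5 |
| 0.05 | 0 to 0.82 | 1 to 12.5 |
| 0.10 | 0 to 0.87 | 1 to 13.2 |

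The estimate is zero when the between mean square does not exceed the within mean square. At true ICC 0.05 this has probability P[F(2, 56) ≤ 1/1.789] = 1 − (1 + 0.559/28)^−28 = 0.42. At 0.01 it is 0.57 and at 0.10 it is 0.31.

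**3. Which degrees of freedom.** The 95% interval for a variance runs from df/χ²(0.975) to df/χ²(0.025) times its estimate. With 14 df: 14/26.12 = 0.54 to 14/5.63 = 2.49. With the 2 df behind the between-physician mean square: 2/7.378 = 0.27 to 2/0.0506 = 39.5. The sample-size argument concerns the first range; the ICC depends on the second.

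**4. Primary model, if large-sample limits were used.** A random-intercept model fitted by REML with z limits has error of about 5.2%, 8.8% and 12.0% at ICC 0.01, 0.05 and 0.10 (simulated, one time point, continuous outcome).

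**The case against.** The strongest reply is that this is a feasibility pilot and largely says so. Proposed sample size puts precision above power, the Background states a feasibility objective, and the section on the Data Monitoring Committee calls the trial preliminary and exploratory. With one clinic, and possibly random allocation of patients to physicians, the ICC may be low; at 0.01 the inflation is small (pooled t 6.6%). Some feasibility items, such as sending BP readings by smartphone, exist only in the intervention arm, so no between-arm test applies to them.

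This limits the size of the first point, but the named tests remain wrong for a trial with physicians nested in arm. It does not touch the second, which needs no assumed ICC for its intervals.

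Three stronger readings are tempting, and the text does not support them:

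- **That the primary model's intervals are wrong.** The section names both patient and physician clustering and states neither z limits nor a df method. An analysis plan not shown may hold one. What can be said is that large-sample limits would be unreliable with four clusters.
- **That the secondary model omits the patient level.** The section names physician as random but does not say physician only, and cites the same model reference as the primary section. Within-patient correlation may sit in the residual covariance.
- **That the protocol claims good precision for the between-physician variance.** It ties its precision statement to within-cluster df. The gap is that this statement does not carry over to the ICC.

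**Conclusion.** Two points stand. The between-arm feasibility tests ignore physician, with pooled-t error of about 6.6%, 8.4%, 13% and 21% at assumed ICCs of 0.01, 0.02, 0.05 and 0.10: minor at the low end and material from about 0.05. The plan to determine the next trial's size from the pilot ICC is unsound as stated, because for any observed value from 0.01 to 0.10 the interval runs from about 0 to between 0.75 and 0.87, and the stated sample-size justification does not address this.

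The error rates rest on assumed ICCs and one time point; they are not error rates for the planned longitudinal model of BP control. The ICC intervals assume a normally distributed outcome and equal clusters of 15.

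Lesser points are the Abstract's wording of a test of effectiveness, which is out of line with the rest of the protocol; the status of the primary arm contrast; and the different descriptions of the primary and secondary models. The last needs clarification and is not a shown error.

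**What to change.** 1. **Statistical analyses, Feasibility outcomes.** Drop the chi-square, pooled t and Wilcoxon comparisons. Report arm differences as estimates with limits from a t on the four physician means, 2 df. A REML model with 2 df is not equivalent: where the t on physician means held 5% in simulation, it rejected in only about 0.1% of trials at ICC 0.05 and 0.4% at 0.10.
2. **Proposed sample size.** Limit the precision statement to within-physician variance.
3. **Statistical analyses, Primary outcome measures.** Report the pilot ICC only with its confidence interval, and size the next trial over a range of external ICCs. Present the arm contrast as an estimate, and note that large-sample limits are unreliable with four physicians.
4. **Abstract.** Reword the objective as estimation.
5. **Statistical analyses, Secondary outcome measures.** State that within-patient correlation is modelled, as in the primary section.

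No patients or visits are added. The cost is in rewording, in some changed code, and in much wider intervals: the multiplier rises from 2.00 to 4.30, and most arm differences will be compatible with almost any conclusion. That reflects what four physicians can show.

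### With two physicians per arm, the primary GLMM's usual confidence intervals for the BP difference are too narrow unless the physician ICC is about 0.01 or less

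*Protocol article*

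**What the plan says.** Trial design describes a cluster randomised trial "with the physician as unit of randomization and patients as unit of analysis" and states that "Each of the four physicians will be recruited and randomly assigned to the intervention or control group by the statistician". The abstract gives the split as "two clusters in the intervention arm and two in the control arm". Proposed sample size sets 15 patients per physician, 30 per arm and 60 in all. It says that "sample size justification focuses on the precision of estimates rather than the power of statistical tests", and that the number per arm was chosen "based on number of degrees of freedom within each cluster".

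Under Statistical analyses, Primary outcome measures, "generalized linear mixed models (GLMM) will be used to compare the two groups with group as primary independent variable", with BP control or BP change as the dependent variable. The models are said to "take into account the effect of clustering, i.e., correlation of repeated measurements within patients clustered within MD (Medical Doctor) provider". The section promises 95% CIs for between-group differences in proportions and slopes, a time-by-intervention term, and an ICC estimate for sizing a later trial. It names no degrees-of-freedom rule, reference distribution or small-sample correction. The Secondary outcome measures analysis names physician as a random effect.

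**The concern.** Treatment arm does not vary within a physician. The error of the arm difference therefore comes from variation between physicians in the same arm, which has 4 − 2 = 2 degrees of freedom. The sample-size section argues from degrees of freedom within clusters (14 per physician, 56 in all), and these do not inform that contrast.

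A mixed model fitted to four clusters has two weak points. The physician variance cannot go below zero and often lands there, after which the model gives the standard error of 60 independent patients. When the variance is positive, it is estimated on 2 df, and a z or 58-df multiplier does not reflect that uncertainty. Either way, the statement that clustering is taken into account promises more than the usual output delivers.

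Precision is the stated product of this pilot, BP is a primary outcome, and a favourable early signal on BP is what would lead to the larger trial. Intervals that are too short would overstate that signal.

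**Working it through.** **Inputs from the article.** 2 arms × 2 physicians × 15 patients = 60, which reproduces the stated total. No SD, ICC, effect size or power target is given, so there is no precision figure to reproduce.

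**Assumptions.** ICC ρ from 0 to 0.20; SBP SD 20 mmHg where a half-width in mmHg is shown; one visit, balanced clusters, no covariates.

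**1. How often the physician variance is zero.** With m = 15, REML gives max(0, (MSB − MSW)/15). It is zero when MSB ≤ MSW, which has probability P[F(2,56) ≤ (1 − ρ)/(1 + 14ρ)]. For F(2,56) this equals 1 − (1 + x/28)^(−28), where x is that ratio. At ρ = 0.05, x = 0.95/1.70 = 0.559 and the probability is 1 − (1.01996)^(−28) = 0.425.

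**2. Type I error at nominal 5%** (400,000 simulated trials per ICC). The standard error is √(V/15), with V = MSB if the variance is positive and the pooled mean square otherwise.

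| ICC | variance = 0 | GLMM, z | GLMM, t on 58 df | physician means, t on 2 df |
|---|---|---|---|---|
| 0 | 63% | 4.0% | 3.7% | 5.0% |
| 0.01 | 57% | 5.3% | 4.8% | 5.0% |
| 0.02 | 53% | 6.2% | 5.7% | 5.0% |
| 0.05 | 43% | 8.9% | 8.3% | 5.0% |
| 0.10 | 31% | 12.1% | 11.4% | 5.1% |
| 0.20 | 19% | 15.3% | 14.7% | 5.0% |

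Interval coverage is 100% minus these figures: with z, 91.1% at ICC 0.05 and 87.9% at ICC 0.10. Most of the excess comes from trials in which the variance is zero. At ICC 0.05 the z error is 14.8% in those and 4.5% in the rest: 0.427 × 14.8% + 0.573 × 4.5% = 8.9%.

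**3. Binary BP control.** Random-intercept logistic GLMM, Wald z, 1,500 trials per setting, control rate 0.4 or 0.6. At latent ICC 0.01, 0.05 and 0.10 the variance is zero in 82–84%, 68–73% and 58–60% of trials, and type I error is about 5%, 9–11% and 12–13%.

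**4. Width.** SE = 20 × √(2(1 + 14ρ)/30). At ρ = 0.05 this is 20 × √(3.4/30) = 6.73 mmHg.
- z: 1.960 × 6.73 = 13.2 mmHg.
- t on 2 df: 4.303 × 6.73 = 29.0 mmHg.
- Ignoring physicians: 1.960 × 20 × √(2/30) = 10.1 mmHg.

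The 29.0 has MSB at its expected value. In a real trial MSB varies as χ²(2)/2, with 10th and 90th percentiles of 0.105 and 2.303 times its expectation. The reported half-width then runs from 29.0 × √0.105 = 9.4 to 29.0 × √2.303 = 44.0 mmHg. In about 11% of trials it is shorter than 10.1 mmHg.

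**5. A remedy that fails.** Using t on 2 df but leaving the variance truncated at zero rejects in 0.02%, 0.09% and 0.4% of null trials at ICC 0.02, 0.05 and 0.10, which is grossly conservative.

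**6. The ICC as a planning input.** At a true ICC of 0.05, the estimate from four physicians has a 95% sampling range of 0 to 0.29.

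**The case against.** The strongest reply is that the article does not commit the error. It specifies a model with patients clustered within physician and names no z reference, residual-df rule or software. A containment or between-within rule would give 2 df in the same model, and such detail is commonly left to an analysis plan that is not shown. This stands, and it limits the point. What remains is that the four-physician design and the unqualified statement about clustering are both fixed in the article. Moreover, step 5 shows that changing the df rule alone does not repair the inference.

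A reader might infer from "with the physician as unit of randomization and patients as unit of analysis" that patients will be analysed as independent. The article does not support that. This is ordinary wording for patient-level data in a multilevel model, and the analysis section models the physician.

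The harm also depends on an unstated ICC and is negligible at 0.01 or below. Allocation and concealment has consenting patients randomly allocated to the clusters. If followed, this would remove patient mix, though not differences in care, as a source of ICC. Physicians would still be nested in arm, so the 2 df remain.

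The calculation covers one visit. A physician random intercept cancels from group-by-time contrasts, so these are less exposed, and their error was not computed. They remain open to physician-by-time variation, which the plan does not mention.

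Finally, this is a pilot sized for precision, with no numerical efficacy rule and no P-value planned for the primary outcomes. That lowers the severity, but not the need for valid intervals.

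**Conclusion.** The point holds in a conditional form. The arm contrast has 2 df. Under the usual z or residual-df reference, the 95% CIs for the BP difference at a visit are too narrow unless the physician ICC is about 0.01 or less. Type I error is about 6%, 9% and 12% at assumed ICCs of 0.02, 0.05 and 0.10, and 4% to 5% at ICC 0 to 0.01. The figures rest on one visit and a normal outcome; the logistic check points the same way.

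The stronger reading, that the plan ignores clustering or that its BP comparison is bound to be overconfident, is not supported, because the reference distribution and the ICC are both unstated. For a precision-sized pilot this should be fixed, but it does not undermine the trial.

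**What to change.** - Keep the GLMM for point estimates.
- Base the 95% CI for the group difference at each visit on a two-stage analysis: one summary per physician, then a t interval on 2 df from the four summaries. An equivalent model in which the physician variance is not truncated at zero would also serve. Do not combine 2 df with a truncated variance.
- For group-by-time, apply the same two-stage approach to physician-level changes, because physician-by-time variation is not otherwise modelled.
- Show the four physicians' results side by side, and label the BP comparison and the ICC estimate as descriptive.
- In Trial design, state that patient-level data are analysed but that inference on the arm effect is at physician level.

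This changes wording and analysis only; recruitment and conduct are untouched. The price is much wider intervals (expected half-width about 29 against 13 mmHg at the assumed SD and ICC 0.05) that vary greatly from one trial to the next (about 9 to 44 mmHg, 10th to 90th percentile). The report should say so, because any single interval may by chance look precise.
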